### Blinding

Given the nature of the intervention, the trial cannot be blinded. Although data collectors will be independent of those delivering treatment, they will be able to deduce the randomization status of participants when they see the supplies required for treatment. Similarly, statisticians conducting the analysis cannot be blinded. To minimise bias, an *a priori* analytical plan will be defined as the intervention is in progress and will be adhered to.

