### Statistical methods

Statistical support will be provided by the KEMRI-Wellcome Trust Programme in Kilifi, Kenya. A detailed Statistical Analysis Plan will be developed in 2014-15 while the intervention is in process, and will be approved by the Trial Steering Committee. The main analysis will be a test of mean number of ADLA events by each arm over the observation period.

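### The reason given for not blinding the analysing statisticians does not apply to them, and the substitute safeguard sets no limit on seeing outcomes by arm

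*Protocol article*

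**What the plan says.** The Blinding section opens with "Given the nature of the intervention, the trial cannot be blinded". It says that data collectors are separate from those who deliver treatment, but that "they will be able to deduce the randomization status of participants when they see the supplies required for treatment". It continues: "Similarly, statisticians conducting the analysis cannot be blinded". To limit bias it promises that an *a priori* "analytical plan will be defined as the intervention is in progress and will be adhered to".

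Statistical methods gives the same timing and adds an approval step: "A detailed Statistical Analysis Plan will be developed in 2014-15 while the intervention is in process, and will be approved by the Trial Steering Committee". It fixes the main comparison in one sentence: "The main analysis will be a test of mean number of ADLA events by each arm over the observation period".

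**The concern.** The word linking the two statements treats the analyst's position as the same as the data collector's. It is not. A data collector enters the home and sees soap, ointment, bandages and shoes. An analyst sees rows and columns, and the arm column can carry an uninformative code. The article therefore declares a standard safeguard impossible on grounds that do not reach it.

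This matters because the replacement safeguard depends on what its authors can see. A plan drafted during follow-up protects against data-driven choices only if those drafting it do not see outcomes by arm. The endpoint is a self-reported count in an open trial. Some choices that could influence the result, such as how daily diary marks become episodes or how incomplete follow-up is treated, are properly left to the SAP. If they were made with knowledge of results by arm, adhering to the plan afterwards would give no protection.

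**Working it through.** The point contains no figure of its own, so the check sets the sections side by side.

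1. **Ground for the claim.** Blinding gives two reasons: the nature of the intervention, and supplies visible to data collectors. Neither concerns the dataset, and no reason specific to the analysis is given.

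2. **Overlap in time.** Table 1 and Outcomes and measurement define the primary endpoint as all ADLA episodes over 12 months of follow-up. Table 3 schedules diary data at 3, 6, 9 and 12 months. Blinding and Statistical methods both place the writing of the plan within the intervention period. The plan is therefore written while the primary outcome accrues.

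3. **Route of the data.** Data management describes weekly uploads to a system run by the Kilifi facility. Randomisation has statisticians at the KEMRI-Wellcome programme prepare the list, and Statistical methods has that programme give statistical support. This places the allocation list, the data and the analysis within one organisation. It does not show that one person has all three, and no separation of roles is described.

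4. **What is fixed and what is open.** Fixed: the endpoint and a comparison of mean counts by arm. Not given in the article: the derivation of episodes from diaries, the handling of partial follow-up, and the identity of the four confounders mentioned under Sample size. Leaving these to a SAP is normal. They are listed only to show what the SAP authors still decide.

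5. **How much outcome data could exist while the plan is written.** Assume that visits are counted from the start of the intervention and that the plan is finished by the end of 2015 and before the intervention ends.
   - Start in December 2014 (Intervention section): the 3-, 6- and 9-month rounds fall in March, June and September 2015, so up to three rounds.
   - Start in May 2015 (Abstract): the 3- and 6-month rounds fall in August and November 2015 and the 9-month round in February 2016, so up to two rounds.

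   The article gives both dates, so the range is two to three rounds. These are rounds collected, not rounds known to have been seen by arm.

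6. **Effect of the change on the design.** The stated sample size uses a mean of 5.6, an SD of 4.9, a 28% reduction, 90% power and alpha 0.05 (two-sided assumed). With a difference of 0.28 × 5.6 = 1.568, n = 2 × [4.9 × (1.960 + 1.282) / 1.568]² ≈ 205.2, rounded up to 206 per arm, as stated. Then 206 × 1.4 / 0.85 = 339.3, rounded to 340 per arm and 680 in total. No term depends on who knows the allocation at analysis, so masking the analyst changes nothing here.

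**The case against.** A reader might infer that the statisticians hold the allocation and watch arm-labelled outcomes arrive while they draft the plan. The document does not say so. Sharing an institution is not sharing a login, and being unblinded when conducting the analysis is not the same as seeing results by arm while writing the SAP. Assessment of quality states that no interim analyses are planned, so no planned comparison by arm precedes the final one. The Steering Committee must approve the SAP, and the endpoint and main test are already set. Writing a SAP during follow-up is not in itself an error. Sign-off timing and custody of the list are matters that a condensed article may leave to a fuller document. All of this stands, and it limits the point.

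A reader might also suppose that masking plus an earlier lock would eliminate the bias at no cost. It would not. Diaries are collected monthly in the treated arm, whereas after the first month only a random 10% are checked in controls (Outcomes and measurement). Intervention-related adverse events are actively elicited each month only in the treated arm (Safety). Completeness of the primary data might itself reveal a coded arm. Episodes are also self-reported, and diary-recall discrepancies are reconciled with data collectors who can deduce the arm. Analyst masking does not touch that.

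The objection does not rescue the sentence itself. It is a positive statement that blinding is impossible, not a detail left out, and an unseen SAP could not make its reasoning valid. Committee approval does not restrict what the drafters see, and the absence of planned interim analyses is not a rule against access by arm. With no interim analysis and no DSMB, the article gives the analyst no need for outcomes by arm before the SAP is signed.

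**Conclusion.** The point holds in a limited form. The claim that analysts cannot be blinded does not follow from the reasons given. The plan offered in its place is written while the primary outcome accrues, with no stated bar on its authors seeing results by arm. It is the combination that is weak: either element alone would matter less.

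The document does not support the conclusion that anyone actually sees outcomes by arm before the plan is final, or that any analytic choice is compromised. The size of the bias cannot be quantified from it. The two to three rounds of data that might exist by then rest on the assumptions stated with that count and on which start date applies. The weight is minor to moderate: a cheap improvement to a stated rule, not a flaw that invalidates the trial. It would reduce analyst-driven bias only.

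**What to change.** Replace the sentence on statisticians in the Blinding section with:

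> The analysing statistician works with masked arm codes, on a dataset without arm-revealing variables (adherence, meeting attendance, monthly diary-check records, CPA-elicited adverse events), until the primary analysis code is final. The SAP, including the derivation of episodes from diaries, is signed and dated before any outcome data are released by arm.

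Add a clause to Statistical methods that ties Steering Committee approval to that same moment, so that the two sections agree.

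The cost is small: a filtered data export, and the allocation code kept from the analyst by existing staff of the unit. Masking may be imperfect because of the different diary handling by arm. The sign-off rule still protects the analysis plan in that case.

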### Study visits

A timeline of the study is presented in Table 3.

**Table 3 Tab3:** Study timeline

	Before enrolment	Enrolment	Baseline	Visit 1	Visit 2	Visit 3	Visit 4 close-out
Timepoint		*-t* _*1*_	0	*3 months*	*6 months*	*9 months*	*12 months*
Screening	X						
GIS mapping	X						
Potential willingness to participate	X						
Inclusion and exclusion criteria	X	X					
Consent		X					
Randomisation			X				
Socio-demographic			X				X
Economic		X	X		X		X
ADLA (recall)		X	X				
ADLA diary				X	X	X	X
SAEs			X	X	X	X	X
DLQI			X	X	X	X	X
WHO-DAS II			X		X		X
Stigma scale			X		X		X
Clinical stage			X	X	X	X	X
Mossy lesions			X		X		X
Foot and leg Circumference			X		X		X
Interdigital lesions			X		X		X
Foot care and hygiene intervention (immediate treatment group)*							

*Monthly intervention meetings

### Intervention

The intervention in this trial is podoconiosis lymphoedema hygiene and foot-care management. This consists of monthly group meetings with instruction and practical demonstration of foot hygiene and foot care by Community Podoconiosis Assistants (CPAs), supporting daily self-treatment. In outline, ‘foot hygiene’ comprises soaking feet, washing with soap, rinsing with clean water, drying and application of emollient. ‘Foot care’ includes supervised use of single-layer, non-elastic bandages for disease stages ≥3; foot and calf exercises; instruction to practice foot hygiene daily at home; instruction to elevate the foot of the bed or areas slept on; instruction to use socks and shoes during waking hours. Those randomised to immediate treatment will receive a hygiene and foot-care intervention from December 2014 for one year, while those randomised to the control arm will be followed through 2014 and will be offered the intervention in 2015, unless it has been shown to be ineffective or harmful.

The trial interventions are described in Table 4.

**Table 4 Tab4:** Trial intervention

Action	Necessary items
Soak for 15 minutes	Bowl of water
Wash with soap	Named brand (GIV international white)
Apply emollient	Each patient will be issued with Whitfield’s ointment (2 tubes of 20 gm for a period of 1 month)
Apply bandages	For stage ≥3 disease; two short-stretch (<80 % stretch) bandages, spiral from foot, overlap 50 %, continue 8-10 cm above oedema
Elevation and exercises	Ankle rotation exercises.
	Elevate foot end of sleeping mattress, if used
Use socks and shoes	Temporary (tyre) shoes if bandages issued
	One pair robust, closed shoes and two pairs of socks after 3 months of treatment

Each patient randomised to the treatment arm will be allocated one bar of toilet soap (GIV international white) every month, and rate of use will be monitored at monthly meetings. In addition, patients will have dispensed 40 gm of Whitfield’s ointment sufficient for daily application for one month, will be asked to bring used tubes with any remaining ointment to their group meeting each month, and excess ointment will be recorded. Patients with stage 3 and greater podoconiosis will each receive two short-stretch (<80 % stretch) bandages for each affected foot, one to be worn while the other is being washed and dried. Under likely home conditions, it is anticipated that bandages will need replacement after approximately 6 months. However, the condition of the bandages will be checked at monthly group meetings, and replacements given as required. Patients receiving bandages will also be given temporary, loose-fitting shoes at the enrolment visit. All patients’ feet will be measured at 3 months (once the majority of the swelling is anticipated to have subsided), and they will be given a pair of strong, closed ‘trainer’ or leather shoes and two pairs of socks. Patients will be encouraged to wear shoes all day, every day, no matter what their activities, and will be shown how to clean and care for their shoes and socks. We anticipate that high quality shoes will last for the full year of the trial, while socks will require replacement after 6 months, but the condition of shoes and socks will be monitored through the monthly meetings. Soap, Whitfield’s ointment and bandages will be kept out of the reach of children in a plastic treatment box. Standard operating procedures fully describe the hygiene products, their storage and application to assure consistency between participants, healthcare workers and study visits.

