**Methods/Design:**

This is a pragmatic, individually randomised controlled trial. We plan to randomly allocate 680 podoconiosis patients from the East Gojjam Zone in northern Ethiopia to one of two groups: ‘Standard Treatment’ or ‘Delayed Treatment’. Those randomised to standard treatment will receive the hygiene and foot-care intervention from May 2015 for one year, whereas those in the control arm will be followed through 2015 and be offered the intervention in 2016. The trial will be preceded by an economic context survey and a Rapid Ethical Assessment to identify optimal methods of conveying information about the trial and the approaches to obtaining informed consent preferred by the community. The primary outcome will be measured by recording patient recall and using a simple, patient-held diary that will be developed to record episodes of acute attacks. Adherence to treatment, clinical stage of disease, quality of life, disability and stigma will be considered secondary outcome measures. Other outcomes will include adverse events and economic productivity. Assessments will be made at baseline and at 3, 6, 9 and 12 months thereafter.

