### Endpoints

The endpoints for this trial are listed in Table 1.

**Table 1 Tab1:** Endpoints

	Endpoint details
Primary endpoint	Cumulative incidence of ADLA (total number of incident episodes over the 12-month follow-up period).
Secondary endpoints	Adherence to treatment
	Foot washing, use of ointment, use of bandages, elevation, exercises, use of socks and shoes.
	Clinical outcomes:
	Clinical stage of disease^a^
	Lower leg and foot circumferences^b^
	Presence of mossy changes
	Wounds and inter-digital lesions;
	Duration of ADLA days
	Social outcomes:
	Quality of life^c^
	Perceived stigma^d^
	Economic outcomes:
	Economic productivity^e^

ADLA, acute dermatolymphangioadenitis

^a^Using a scale specifically developed for use in podoconiosis patients [22]

^b^Measured in centimetres at mid-calf and mid-foot

^c^Using validated Amharic translation of Dermatology Life Quality Index [23] and WHO Disability Assessment Schedule-II (WHODAS-II)

^d^Using scale developed to measure stigma among podoconiosis patients (24)

^e^Other measures of economic vulnerability found to be related to podoconiosis in economic context survey

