### Assessment of quality

The trial will be monitored by staff at the KEMRI-Wellcome Trust Programme’s Kilifi Clinical Trials Facility (KCTF), who will perform on-site and database monitoring. The approach for trial monitoring will include mentoring and supporting the trial staff and healthcare workers, working closely with them before, during and after the trial to help achieve an ethical, safe and accurate trial that answers the questions set within this protocol.

Pre-study start site visits will occur before the first participant is enrolled. Standard Operating Procedures (SOPs) will be developed followed by a study initiation visit that will be conducted by the study coordinator and supported by the monitoring staff from Kilifi. Here, the SOPs will be used to ‘walk’ through the study with everyone involved. All trial staff will be trained and certified for Good Clinical Practice (ICH-GCP). A trial monitoring plan will be written and signed off by the Trial Steering Committee. This will detail how many monitoring visits are planned and specify the key data points that require checking against source data. The fact that the products being used are known and safe, the trial is essentially open and there are no plans for interim analyses, internal monitoring being performed by KCTF staff [20] is in accord with WHO guidance [21].

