## Trial status

The Rapid Ethical Assessment, the economic context survey and validation of the patient-held diary have all been completed. Recruitment for the trial commenced on 8 October 2014.

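### The Abstract and the Intervention section give incompatible calendars, and the control follow-up stated in the Intervention section cannot deliver the 12-month primary endpoint

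*Protocol article*

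**What the plan says.** The Abstract (Methods/Design) says that the treated arm "will receive the hygiene and foot-care intervention from May 2015 for one year". For the comparison group, its plan is that "those in the control arm will be followed through 2015 and be offered the intervention in 2016".

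The Intervention section says that the treated arm "will receive a hygiene and foot-care intervention from December 2014 for one year". For the comparison group, its plan is that "those randomised to the control arm will be followed through 2014 and will be offered the intervention in 2015". It adds a proviso to the offer: "unless it has been shown to be ineffective or harmful".

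Table 1 defines the primary endpoint as the "total number of incident episodes over the 12-month follow-up period", and the Outcomes section repeats the 12-month period. Table 3 places randomisation at time 0 and close-out (Visit 4) at 12 months, with the same visits for both arms. Trial status reports: "Recruitment for the trial commenced on 8 October 2014". On early looks at the data, Assessment of quality says "there are no plans for interim analyses".

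No sentence ties the offer to controls to their 12-month visit.

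**The concern.** Two current passages of one protocol date the same trial differently, and they are not a simple shift of each other. Treatment start differs by 5 months, but the control years differ by a full year. The amount of untreated control follow-up therefore differs too.

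Neither calendar, taken literally, states 12 months of control follow-up alongside the treated arm. The primary comparison is of episode counts over 12 months, and the sample size assumes a full-year difference between treated and untreated patients. If controls are followed for less time, or start treatment inside the window, the arms no longer supply that comparison.

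**Working it through.** **Step 1. The plan's own sample size.** Inputs from the Sample size section: mean 5.6, SD 4.9, reduction 28 %, power 90 %, alpha 0.05 (two-sided assumed, since sidedness is not stated).

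- n per arm = 2 × [SD × (1.960 + 1.282) / difference]²
- With difference 0.28 × 5.6 = 1.568, n = 206, as stated. With 5.6 − 4.0 = 1.6, n = 198.
- 206 × 1.4 / 0.85 = 339.3, hence 340 per arm and 680 in total.

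The figure reproduces and is not in dispute. It takes annual episode rates, so it presumes a 12-month contrast.

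**Step 2. Calendar arithmetic, counted from treatment start.** The month is given but not the day, so each entry is a range from the first to the last day of that month.

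| | Intervention section | Abstract |
|---|---|---|
| Treatment starts | 1–31 Dec 2014 | 1–31 May 2015 |
| 12-month window closes | 1–31 Dec 2015 | 1–31 May 2016 |
| Stated control follow-up ends | 31 Dec 2014 | 31 Dec 2015 |
| Control follow-up inside the window | 0–30 days | 214–244 days (7.0–8.0 months) |
| Window remaining when the offer year opens | 11–12 months | 4–5 months |

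**Step 3. Can a different clock rescue either calendar?**

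- Intervention section, counted from the first day of recruitment: 8 October to 31 December 2014 is 84 days (2.8 months). Reading the phrase as the whole of 2014 does not help, because recruitment had not begun before October.
- Abstract, counted from a baseline taken between 8 October and 31 December 2014 (an assumption): follow-up to the end of 2015 gives controls at least 12 months. Treatment starting on 1 May 2015 would then leave the treated arm untreated for the first 4.0 to 6.7 months of that window.

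**Step 4. Worst-case illustration of overlap.** Assumptions not in the documents: every control is offered treatment on 1 January, all take it up, and the full effect is immediate. The 12-month difference becomes 1.6 × (untreated months / 12). SE = 4.9 × √(2/n). Power is the chance of a significant result favouring treatment. Two values of n are shown: 206 per arm, and 340 × 0.85 = 289 per arm if the 40 % confounder allowance counts as usable sample.

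| Untreated control months | Difference | Power, n = 206 | Power, n = 289 (SE 0.4076) |
|---|---|---|---|
| 12 (no overlap) | 1.60 | 91 % | 97.5 % |
| 8 (Abstract, start 1 May) | 1.07 | 60 % | 74 % |
| 7 (Abstract, start 31 May) | 0.93 | 49 % | 63 % |
| 1 (Intervention section, start 1 Dec) | 0.13 | 5 % | 5 % |
| 0 (Intervention section, start 31 Dec) | 0 | 2.5 % | 2.5 % |

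**Step 5. How far the illustration depends on its assumptions.** With 289 per arm, 90 % power needs a difference of 3.242 × 0.4076 = 1.32, which is 1.32 / 1.6 × 12 = 9.9 untreated months. Under the Abstract's dates with a 1 May start, offers averaging March 2016 or later would keep 90 %. With January offers but 50 % uptake (assumed), the difference is 1.07 + 0.5 × 1.6 × 4/12 = 1.33, and power is again about 90 %.

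**The case against.** The strongest reply is that early treatment of controls is inferred from calendar years alone, and that the rest of the protocol points the other way. The offer is dated only by year. Under the Abstract, an offer between June and December 2016 falls wholly after the window. The proviso in the Intervention section withholds the offer if the intervention proves ineffective or harmful. With no interim analysis, ineffectiveness could be shown only by the final analysis, after month 12. The Adverse event monitoring section commits to running the trial to full power, and Table 3 lists the intervention for the immediate group only. The relative schedule of 3, 6, 9 and 12 months is consistent throughout. On this view the Intervention section simply carries dates that were not updated.

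Much of this stands. A reader might infer that the plan treats controls inside the endpoint window under both calendars, so that the stated power no longer applies. The documents do not support that: they allow an early offer but do not schedule one, and the proviso suggests an offer after the trial. The immediate, complete effect assumed in the illustration is also unsupported: closed shoes are issued only after 3 months, and the Discussion reports slower change in leg circumference and stage, though not in acute attacks.

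The reply does not remove the contradiction between the two passages. Nor does it make the control follow-up in the Intervention section fit 12 months. The apparent intent to offer treatment after close-out is nowhere stated.

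**Conclusion.** This is an internal inconsistency, wrong as written and more than clerical, because the dates govern how long controls are observed untreated.

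- **Certain:** the two calendars conflict, by 5 months in treatment start and by one year in the control dates.
- **Certain:** the control follow-up in the Intervention section (0 to 1 month from treatment start, 84 days from first recruitment) cannot yield the 12-month endpoint.
- **Possible, not certain:** under the Abstract, the stated control follow-up covers 7 to 8 of 12 months and the offer year opens 4 to 5 months early. Whether any control would be treated inside the window is not stated.
- **Direction only:** overlap would shrink the contrast on which the sample size rests. The power figures above bound the loss under extreme assumptions and are not a forecast.

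The documents do not show which dates are correct, and this review does not choose between them.

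**What to change.** Reconcile the Abstract and the Intervention section with each other and with Table 3, so that one calendar remains in which both arms are observed concurrently over the same 12 months to Visit 4. Add one sentence stating when controls are offered the intervention relative to Visit 4. The choice of dates is for the sponsor and investigators.

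A rule that closes the counting window in both arms as soon as any control starts treatment is not advised: one early starter could truncate a fixed 12-month endpoint for the whole trial.

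The cost is a wording correction in two places and one added sentence. The sample size stands if the reconciled calendar preserves the full 12-month contrast. If it does not, the sample size assumptions need to be revisited.
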